### Intervention

The decision on treatment will be left to the discretion of the attending surgeon. The choice will be between operative and non-operative treatment. Also, the rehabilitation after treatment will not be standardized, but will be provided as in real life. Although this may create some heterogeneity across groups, it will improve the generalizability of the study results.

If a surgeon decides to operate the patient, the choice between plate osteosynthesis or intramedullary nailing will be left to the treating surgeon. No restrictions will be applied to the approach for reduction and fixation of the fracture, *e.g.*, open or closed, antegrade or retrograde. The type and brand of the materials as well as the use of cerclage wires and other elements of the surgery will be left to the surgeon, local availability and expertise. Critical elements of the operative treatment will be recorded (*e.g.*, type of implant, identification of the radial nerve, surgical approach, operative delay, duration of surgery) and the effect on outcome will be assessed.

In order to maximize generalizability, the type of non-operative treatment will also be left to the attending surgeon. Usually it consists of a splint, plaster, collar and cuff or hanging cast for 1–2 weeks, followed by a Sarmiento brace for 4–6 weeks. Critical elements of this treatment will be recorded and the effect on outcome will be assessed.

Due to a lack of evidence favoring a particular approach, the physical therapy and rehabilitation program will be recorded but not standardized. This will improve generalization of the study results.

### Outcome measures

The Disabilities of the Arm, Shoulder and Hand (DASH) outcome measure will serve as primary outcome measure. The DASH is a validated 30-item, self-report questionnaire designed to help describe the disability experienced by people with upper-limb disorders and also to monitor changes in symptoms and function over time [34,35]. It is scored in two components: the disability/symptom section (30 items, scored 1–5) and two optional Work and high performance Sport/Music modules (each 4 items, scored 1–5). The DASH disability/symptom score is a summation of the responses to 30 questions on a scale of 1 to 5, with an overall score ranging from 0 (no disability) to 100 (severe disability). At least 27 of the 30 items must be completed for a score to be calculated. The DASH optional modules aim to measure symptoms and function in athletes, performing artists and other workers whose jobs require a high degree of physical performance. These optional models are scored separately and each contains four items, scored 1–5. All items must be completed for a score to be calculated.

The secondary outcome measures are:

• Constant score

• Pain level at both sides (VAS)

• Range of Motion of the shoulder and elbow joint at both sides

• Rate of complications

• Rate of secondary interventions

• Time to resumption of work and other activities of daily living

• Health-related quality of life: SF-36 and EQ-5D

• Radiographic healing

• Cost of health care use and production loss

• Cost-effectiveness

The Constant score reflects both function and pain [36]. This scoring system consists of four variables that are used for assessing shoulder function. The right and left shoulder are assessed separately. The subjective variables are pain (15 points), activities of daily living (ADL; *i.e.*, sleep, work, recreation/sport; 10 points), and arm positioning (10 points), which give a total of 35 points. The objective variables are range of motion (ROM; 40 points) and strength (25 points), which give a total of 65 points. ROM includes forward flexion (10 points), lateral elevation (10 points), external rotation related to the head (10 points) and internal rotation related to the spine column (10 points). ROM will be measured with a goniometer. Strength of abduction will be measured using a calibrated spring balance.

Pain level will be determined using a 10-point Visual Analog Scale (VAS), in which 0 implies no pain and 10 implies the worst possible pain.

The range of motion (ROM) of the shoulder (*i.e.*, abduction and forward flexion) and the elbow joint (*i.e.*, flexion and extension) will be measured using a goniometer. Both sides will be assessed separately, and the loss of ROM will be calculated.

Complications will be recorded from medical charts. Complications may include: 1) surgical site infection; 2) wound dehiscence; 3) skin problems (*e.g.*, skin at risk, skin necrosis); 4) dystrophia; 5) radial nerve palsy; 6) malunion; 7) implant failure (screw breakout); 8) cuff pathology; 9) secondary fracture dislocation; or 10) non-union. Non-union is defined as a failure to heal at twenty-six weeks post fracture with no progress towards healing seen on the most recent radiographs [37].

Secondary intervention within one year of initial treatment to promote fracture healing, relieve pain, treat infection, or improve function will be recorded from medical charts. Interventions will be categorized as: 1) osteosynthesis with or without bone grafting; 2) implant exchange with or without bone grafting; 3) implant removal; 4) incision and drainage for superficial surgical site infection; or 5) incision and drainage for deep surgical site infection. The indication and admission duration for all intervention will also be recorded.

Presence of radiographic healing will be determined using X-rays. Fracture consolidation is defined when one of the three criteria listed is present; 1) bridging of fracture by callus/bone trabeculae or osseous bone; 2) obliteration of fracture line/cortical continuity; or 3) bridging of fracture at three out of four cortices.

The time to resumption of work and activities of daily living will be recorded using a custom-made questionnaire.

The Short-Form 36 (SF-36) is a validated multi-purpose, health survey with 36 questions, representing eight health domains that are combined into a physical and a mental component scale [38]. The Physical Component Summary (PCS) combines the health domains physical functioning (PF; 10 items), role limitations due to physical health (RP; 4 items), bodily pain (BP; 2 items), and general health perceptions (GH; 5 items). The Mental Component Summary (MCS) combines the health domains vitality, energy, or fatigue (VT; 4 items), social functioning (SF; 2 items), role limitations due to emotional problems (RE; 3 items), and general mental health (MH; 5 items). Scores ranging from 0 to 100 points are derived for each domain, with lower scores indicating poorer function. These scores will be converted to a norm-based score and compared with the norms for the general population of the United States (1998), in which each scale was scored to have the same average (50 points) and the same standard deviation (10 points).

The EuroQol-5D is a validated questionnaire for measuring health-related quality of life [39,40]. Its use is recommended for assessing quality of life in trauma patients, especially for economic assessments [41,42]. The EQ-5D descriptive system consists of five dimensions of health (mobility, self-care, usual activities, pain/discomfort and anxiety/depression). Scores are converted to a utility score ranging from zero to one, with lower scores indicating poorer quality of life. The EQ VAS records the respondents self-rated health status on a vertical (0–100) visual analog scale.

The cost-effectiveness analysis will be performed from a societal perspective and will include costs for health care and production losses. Patients will be asked to complete a custom-made questionnaire that contains detailed information on both items. Health care costs will include general practice care, medical specialist care, nursing care, physical therapy, hospitalization, medication, home care, and other costs directly associated with diagnosis, treatment, and rehabilitation.

In addition to the outcome variables mentioned above, the following data will be collected:

a) Intrinsic variables (baseline data): age, gender, American Society of Anesthesiologists’ ASA classification, tobacco consumption, alcohol consumption, comorbidities (including osteoporosis), dominant side, and medication use.

b) Injury related variables: affected side, mechanism of injury, fracture classification according to the AO classification system, additional injuries, and admission duration.

c) Intervention-related variables: time between injury and start of treatment, days of collar and cuff, sling or plaster, time between injury and start of physical therapy, and number of physical therapy sessions.

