## Background

Humeral shaft fractures are associated with a profound temporary (in elderly sometimes even permanent) impairment of independence and quality of life. Fractures of the humeral shaft account for 1-3% of all fractures [1]. The cumulative incidence shows a peak in the working population (14.5/100,000 person years) as well as in the elderly (60/100,000) [1-3].

Humeral shaft fractures can be treated operatively or non-operatively. Operative treatment is mostly performed by intramedullary nailing, plate osteosynthesis, or external fixation. Non-operative immobilization is mostly done with a functional (Sarmiento) brace [4]. Operative and non-operative treatment strategies both have their pros and cons. Operative fracture fixation allows for early mobilization, which may lead to earlier functional recovery and reduced pain. However, surgical complications and fixation failure may occur [5]. Non-operative treatment may be associated with more pain (as the fracture is not stabilized) and discomfort (due to pain and immobilization) in the first weeks and may be associated with a higher malunion risk due to the lack of fracture re-alignment [6,7]. Longer immobilization may delay functional recovery.

Complications of operative and non-operative treatment overlap and data are lacking to determine treatment relatedness. Non-union occurs in 15-30% after operative treatment [5] versus 2-23% after non-operative treatment (for which most patients require secondary surgical treatment) [6,7]. The most feared disabling complication is radial nerve palsy, occurring in 2-17% of all patients [8-10]. A systematic review (n = 4,517 patients) reported an average radial nerve palsy of 11.8%. Although 70% recover spontaneously, the palsy was permanent in 12% of cases accounting for a substantial impairment and costs [9].

Regaining function is extremely important from a patient and societal perspective. From the few retrospective and prospective case series published, each using other outcomes, better functional outcome is expected after operative treatment [8,11-17].

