### Recruitment and consent

Eligible persons presenting to the ED with a humeral shaft fracture will be informed about the trial at the ED. After an explanation of the study, they will receive information and a consent form from the attending physician, the clinical investigator, or a research assistant. Patients meeting all inclusion criteria and none of the exclusion criteria will be included while they are still at the ED or at the time of their first outpatient visit.

As with many surgical trials, patients and surgeons cannot be blinded for treatment. In order to reduce bias, a research physician or research assistant will perform the follow-up measurements using a standardized protocol. Radiographs can also not be blinded for treatment; however, evaluating radiographs in duplicate by two trauma surgeons independently will improve reliability of fracture healing assessment. In case of disagreement they will discuss the results until they reach consensus. Finally, the analysis will be performed by a statistician without knowledge of treatment.

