At each clinical follow-up visit, anterior-posterior and lateral radiographs are generally routinely obtained. All images available from three months onwards will be analyzed. Apart for the 6-month follow-up, during which X-rays are needed for assessing signs of nonunion, local radiographical protocols will apply. For this reason, the follow-up at six month should not be done earlier. In case no radiographic healing is seen at six months, an X-ray at 12 months is also required. At the last visit, the surgeon or researcher will also document any secondary intervention that is planned for the patient.

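### Malunion is taken from hospital charts, and the existing duplicate film reading is described for healing only, so detection may differ between hospitals and treatment groups

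*Protocol article*

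**What the plan says.** All places are in the protocol article.

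- **Source of complications (Outcome measures).** "Complications will be recorded from medical charts". The list of ten types ends with "6) malunion; 7) implant failure (screw breakout); 8) cuff pathology; 9) secondary fracture dislocation; or 10) non-union". Non-union and consolidation are defined in that section; malunion is not.
- **Film reading (Recruitment and consent).** "Radiographs can also not be blinded for treatment", but "evaluating radiographs in duplicate by two trauma surgeons independently will improve reliability of fracture healing assessment". Disagreements are settled by consensus.
- **Which films (Study procedures).** "All images available from three months onwards will be analyzed". A six-month film is needed to assess healing and non-union, and a 12-month film is required if no healing is seen by then. Otherwise local imaging protocols apply. Anterior-posterior and lateral views are described as generally routine.
- **Who collects complications (Study procedures and Table 1).** Research staff establish complications at each of the five follow-up visits and verify them in the medical records.
- **Why malunion matters (Background).** Non-operative treatment "may be associated with a higher malunion risk due to the lack of fracture re-alignment".

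**The concern.** Malunion is a finding on film. The trial already has films and two independent readers, yet the stated source for malunion is the chart. The duplicate reading is described for healing, and a fracture can heal in poor alignment. Such a fracture would be consolidated for the readers and would count as a malunion only if the hospital had recorded it as one.

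Recording habits can differ among about 30 hospitals. Treatment is chosen by the surgeon, so those habits may also go along with treatment preference. The propensity score balances patient and fracture characteristics; it cannot repair an outcome that is detected differently in the two groups. At stake is the between-group comparison of malunion, and through it the complication rate, which is one of the secondary outcomes.

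**Working it through.** **1. Is malunion tied to one treatment group?** The Background gives non-union ranges for both treatments (15-30% operative, 2-23% non-operative) and radial nerve palsy for all patients (2-17%). It names surgical complications and fixation failure as risks of operation. Of the ten listed complications, only malunion is linked specifically to non-operative treatment, with a mechanism and in cautious terms.

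**2. Does the film reading capture it?** The three consolidation criteria concern bridging of the fracture, disappearance of the fracture line or cortical continuity, and the number of cortices bridged. None concerns angulation or shortening. The section that introduces the duplicate reading gives healing as its purpose. On the text as it stands, the readers are not said to assess alignment.

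**3. Does ascertainment at the visits close the gap?** In part. Staff ask about complications at five visits, so capture does not depend on the treating surgeon's initiative alone. However, no alignment measurement on film is assigned to them, and verification leads back to the medical record.

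**4. Is non-union in the same position?** Largely not. It has a radiographic definition at 26 weeks, a required six-month film, and rests on the healing assessment that is read in duplicate. The only loose end is that it also stands in the chart-sourced list.

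**5. Size.** The article gives no malunion rate and no chart sensitivity, so there is no figure of the plan to reproduce on this point. What follows is illustration by assumption, with the targeted n = 200 per group.

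Observed rate = true rate × share detected. With d the difference in observed rates and p̄ their mean,

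power = Φ{ [ |d| − 1.96·√(2p̄(1−p̄)/n) ] / √[ (p₁(1−p₁) + p₂(1−p₂))/n ] }.

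| True rate, non-op / op | Share detected, non-op / op | Observed, non-op / op | Difference (points) | Power |
|---|---|---|---|---|
| 15% / 5% | 100% / 100% | 15% / 5% | 10 | 0.92 |
| 15% / 5% | 50% / 50% | 7.5% / 2.5% | 5 | 0.63 |
| 15% / 5% | 50% / 80% | 7.5% / 4% | 3.5 | 0.32 |
| 15% / 5% | 80% / 50% | 12% / 2.5% | 9.5 | 0.96 |
| 10% / 10% | 50% / 80% | 5% / 8% | −3 (spurious) | – |
| 10% / 10% | 80% / 50% | 8% / 5% | +3 (spurious) | – |

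First row: p̄ = 0.10, so [0.10 − 1.96·√(2·0.10·0.90/200)] / √[(0.1275 + 0.0475)/200] = (0.10 − 0.0588)/0.0296 = 1.39, and Φ(1.39) = 0.92.

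As a count for the non-operative group alone: if 5-15% of 200 patients (10-30) have a malunion and charts name 30-60% of them, then 40-70% are missed. That is 10 × 0.40 = 4 to 30 × 0.70 = 21 patients, or 2.0 to 10.5 points of the malunion rate in that group. This is not a between-group bias, because it says nothing about the operative group.

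**The case against.** The strongest reply is that the section on outcome measures must be read with the section on study procedures. Research staff ascertain complications at every visit, and "a research physician or research assistant will perform the follow-up measurements using a standardized protocol". A reader might infer that malunion is recorded only when an unblinded treating surgeon sees fit; the documents do not support that. This part of the reply stands. It narrows the concern without removing it, since no one is described as reading alignment to a common standard.

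A second reply is that an angulation threshold and the fields of a reading form belong in a full protocol, which is not shown. That also stands, so the missing definition is not the finding. The point rests on two choices that the article does state: the chart as source, and healing as the purpose of the duplicate reading. It can be said that naming this purpose does not exclude other readings, and that images from three months are to be analyzed without a stated limit. Even so, the stated source of malunion remains the chart.

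Third, a reader might infer that malunion is the main harm attributed to non-operative treatment. The Background does not say so: it sets malunion beside pain, discomfort and delayed recovery, and says "The most feared disabling complication is radial nerve palsy".

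Fourth, a reader might infer that chart capture tilts the comparison towards non-operative treatment. The documents do not show how completely any complication is charted in either group. Under-recording of implant failure, which can occur only after fixation, would work the other way.

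Finally, the two readers cannot be blinded either. That is correct. The gain is a common standard and two independent readings, not blinding.

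**Conclusion.** The concern holds in a limited form. The article takes malunion from charts at about 30 hospitals and describes its independent duplicate reading for healing only, by criteria that ignore alignment. Malunion may therefore be under-detected, or detected unequally between hospitals or treatment groups. That it is so, by how much, and in whose favour cannot be derived from the documents. The figures shown depend wholly on the assumed rates and detection shares; they show only that the effect could matter and could go in either direction.

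The gap is malunion and, to a lesser degree, implant failure visible on film. A reader might extend it to non-union, but its definition and the six-month film largely cover that outcome; only its source needs to be stated. This concerns one component of a secondary outcome. The primary DASH analysis and the sample size are unaffected. The change is worth making mainly because it is cheap.

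**What to change.** - Have the two existing readers also record alignment on the anterior-posterior and lateral views, and any visible implant failure, on the six-month and later films.
- Classify malunion in both groups from their consensus, using one definition that the sponsor fixes before the readings are made.
- State that non-union is taken from the same consensus reading.
- Keep charts and visit ascertainment for clinical complications and for events before three months.

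Cost: a few fields on the reading form, one definition, and a little more reading time per film. No extra visits or readers are needed, and no extra films where both views are taken as the article describes. The readers remain unblinded, and this limitation should be acknowledged when the results are reported.

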### Study population

All persons aged 18 years or older presenting to the ED with a humeral shaft fracture (AO type 12A or 12B) are eligible for inclusion [33]. The AO type 12C fractures will be excluded due to their low occurrence rate. Humeral shaft fractures are defined as fractures located in the area between the surgical neck and the area immediately above the supracondylar ridge.

Patients meeting the following inclusion criteria are eligible for enrolment:

1. Adult men or women aged 18 years or older (with no upper age limit)

2. A fracture of the humeral shaft, AO class 12A or 12B (confirmed on X-ray)

3. Operation within 14 days after presentation to the ED (if this is the treatment of choice)

4. Provision of informed consent by patient

If any of the following criteria applies, patients will be excluded:

1. Patients with concomitant injuries affecting treatment and rehabilitation of the affected arm

2. Patients with a humeral fracture treated with an external fixator

3. Patients with a pathological, recurrent or open humeral shaft fracture

4. Patients with neurovascular injuries requiring immediate surgery (excl. radial nerve palsy)

5. Additional traumatic injuries of the affected arm that influence upper extremity function

6. Patients with an impaired upper extremity function (*i.e.*, stiff or painful arm or neurological disorder of the upper limb) prior to the injury

7. Retained hardware around the affected humerus

8. Patients with rheumatoid arthritis

9. Bone disorder which may impair bone healing (excluding osteoporosis)

10. Patients incapable of ensuring follow-up (*e.g.*, no fixed address or cognitive impairment)

11. Insufficient comprehension of the Dutch language to understand the rehabilitation program and other treatment information, as judged by the treating physician of researcher

Exclusion of a patient because of enrolment in another ongoing drug or surgical intervention trial will be left to the discretion of the attending surgeon on a case-by-case basis.

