### Study procedures

Clinical evaluation will occur at two weeks (7–21 days window), six weeks (4–8 weeks window), three months (11–15 weeks window), six months (6–7 months window), and 12 months (12–14 months window) after start of treatment [Table 1]. These visits are standard of care for the targeted patient group. At each follow-up visit, the research coordinator or research assistant will ascertain patient status (*i.e.*, adverse events/complications, secondary interventions, etcetera, and will verify information within medical records).

**Table 1 T1:** Schedule of events

**Radiographs & events**	**Screening**	**Enrolment**	**Baseline**	**Post**	**2 weeks**	**6 weeks**	**3 months**	**6 months**	**12 months**
				**surgery**	**(7–21 d)**	**(4–8 we)**	**(11–15 we)**	**(6–7 mo)**	**12-14 mo)**
X-ray	X						X^1^	X^1^	X^1^
Screening	X								
Informed consent		X							
Baseline data			X						
Surgical report form				X					
DASH					X	X	X	X	X
Pain (VAS)					X	X	X	X	X
SF-36					X	X	X	X	X
EQ-5D					X	X	X	X	X
Clinic FU					X	X	X	X	X
Range of motion					X	X	X	X	X
Secondary interventions					X	X	X	X	X
Complications					X	X	X	X	X
Health care consumption					X	X	X	X	X
ADL/work resumption					X	X	X	X	X
Physical therapy					X	X	X	X	X
Constant score						X	X	X	X
Early withdrawal					*	*	*	*	*

^1^X-rays will be taken according to local protocol; all X-rays after three months will be analyzed. The six-month X-ray is needed for assessing fracture healing. If no signs of healing are seen at six months, the 12-month X-ray is also required.

*Only at time of withdrawal.

At each follow-up visit, the range of motion of the shoulder and elbow will be measured using a goniometer by a physician or research assistant. In addition, patients will be asked to complete the questionnaires relating to disability (DASH score including optional modules), pain (VAS), health-related quality of life (SF-36, EQ-5D), health care consumption and production loss. From six weeks onwards, the research coordinator or research assistant will determine the Constant score.

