### Statistical analysis

Data will be analyzed using the Statistical Package for the Social Sciences (SPSS) version 21 or higher (SPSS, Chicago, Ill., USA) and will be reported following the STrengthening the Reporting of OBservational studies in Epidemiology (STROBE) guidelines. Normality of continuous data will be assessed by inspecting the frequency distributions (histograms), and homogeneity of variances will be tested using the Levene’s test.

Descriptive analysis will be performed to report baseline characteristics (intrinsic variables and injury-related variables) and outcome measures for both treatment groups.

For continuous data mean and SD (parametric data) or medians and percentiles (non-parametric data) will be calculated and reported. For categorical data, numbers and frequencies will be calculated and reported for both treatment groups.

Univariate analysis will be performed in order to test the difference in the primary and secondary outcome measures between the operative and the non-operative group. Continuous data such as the DASH score at the different time points (primary outcome) will be tested using a Student’s T-test (parametric data) or a Mann Whitney U-test (non-parametric data). Chi-square analysis will be used for statistical testing of categorical data such as the nonunion rate. A p-value <0.05 will be taken as threshold of statistical significance.

For the primary analysis, a mixed linear regression model will be developed in order to model the relation between different covariates and the DASH score over time. Intrinsic and fracture-related variables that display a p-value <0.5 in univariate analyses will be added as covariate. Similar models will be developed for the Constant, SF-36, and EQ-5D score. Subgroup analysis (*e.g.*, elderly versus <65 years) will be performed.

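### Radial nerve palsy may be present at entry and is also a listed complication, with no onset rule and no named baseline record, so palsy from the injury can enter the complication rate

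*Protocol article*

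**What the plan says.** All of this stands in the protocol article.

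- **Eligibility (Study population).** Exclusion 4 reads "Patients with neurovascular injuries requiring immediate surgery (excl. radial nerve palsy", so palsy from the injury does not bar entry. Exclusion 9 contains the other exempted condition: "Bone disorder which may impair bone healing (excluding osteoporosis".
- **Outcome (Outcome measures).** "Rate of complications" is a secondary outcome. The complications are recorded from medical charts, and the list includes "5) radial nerve palsy; 6) malunion; 7) implant failure (screw breakout". Non-union is given a definition with a time point of 26 weeks. Palsy has no definition and no onset condition.
- **Timing (Study procedures).** At each visit from two weeks after the start of treatment, "the research coordinator or research assistant will ascertain patient status", which includes complications.
- **Data collected (Outcome measures).** The intrinsic variables include "comorbidities (including osteoporosis), dominant side, and medication use". The injury list is "Injury related variables: affected side, mechanism of injury, fracture classification according to the AO classification system, additional injuries, and admission duration". Neither names palsy or nerve status.
- **Adjustment (Statistical analysis).** For the mixed model, "Intrinsic and fracture-related variables that display a p-value <0.5 in univariate analyses will be added as covariate". The propensity score uses an open list: fracture type, age, gender, mechanism of injury, dominance and activity levels.
- **Allocation (Intervention).** Operative or non-operative treatment is the surgeon's choice.

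**The concern.** One condition can be both an entry characteristic and an outcome, and nothing in the text separates the two. A palsy present on arrival may still be present at the two-week visit and be recorded then as a complication.

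Two things are at stake. First, the palsy count would mix harm from the injury with harm from treatment. The Background calls palsy the most feared disabling complication and says that data are lacking to tell which complications are due to treatment. A count without onset cannot supply those data. Second, the study is not randomised, so adjustment is its only protection. If palsy at presentation influences the decision to operate and is not recorded as such, it cannot be balanced or adjusted for.

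**Working it through.** **Plan's own figure.** The DASH assumptions are 16 (SD 16) and 10 (SD 10), a difference of 6. The pooled SD is √((16² + 10²)/2) = 13.34. Then n = 2 × (1.960 + 0.842)² × 13.34² / 6² = 77.6, so 78 per group, as stated. The point does not depend on this figure; it supplies the 6-point yardstick used below.

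**Inputs from the article.** Palsy in 2–17% of patients, average 11.8%; 70% spontaneous recovery; non-union 15–30% after operative and 2–23% after non-operative treatment (Background). Target of 200 per group; 45–55% operated, by fracture subclass and not by palsy (Sample size calculation).

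**Assumed, because not given.** f = share of palsies present at injury; q = share of those patients operated; 20 DASH points per unrecovered palsy. All other palsies are split equally between groups, so there is no treatment effect.

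**Step 1: number of palsies.** 400 × 0.118 = 47.2 (8 at 2%, 68 at 17%).

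**Step 2: inflation of the palsy component.** The factor is 1/(1 − f): 1.33 at f = 0.25, 2 at 0.5 (11.8% counted against 5.9% new) and 4 at 0.75. This needs no assumption about q.

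**Step 3: dilution in the overall rate.** Add non-union only, assumed independent: rate = 1 − (1 − palsy)(1 − non-union), with palsy 11.8% counted or 5.9% new.

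| Non-union | Counted | New palsy only | Ratio |
|---|---|---|---|
| 15% (operative) | 25.0% | 20.0% | 1.25 |
| 30% (operative) | 38.3% | 34.1% | 1.12 |
| 2% (non-operative) | 13.6% | 7.8% | 1.74 |
| 23% (non-operative) | 32.1% | 27.5% | 1.16 |

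The other eight listed complications would lower these ratios further.

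**Step 4: false gap in palsy, operative minus non-operative.** Gap = 400 × 0.118 × f × (2q − 1) / 200. At f = 0.5, 23.6 palsies are present at injury, and the other 23.6 are split 11.8 and 11.8.

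| q | Operative | Non-operative | Gap (points) |
|---|---|---|---|
| 0.20 | 8.26% | 15.34% | −7.1 |
| 0.40 | 10.62% | 12.98% | −2.4 |
| 0.45 | 11.21% | 12.39% | −1.2 |
| 0.50 | 11.80% | 11.80% | 0 |
| 0.55 | 12.39% | 11.21% | +1.2 |
| 0.60 | 12.98% | 10.62% | +2.4 |
| 0.80 | 15.34% | 8.26% | +7.1 |

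With f = 0.5 and q from 0.2 to 0.8, the range is ±1.2 points at 2% overall palsy and ±10.2 at 17%. With f = 1 at 11.8% it is ±14.2, the extreme case. If palsy alone were tested by chi-square at f = 0.5, the chance of p < 0.05 without any treatment effect would be 0.06 at q = 0.45 or 0.55 and 0.60 at q = 0.2 or 0.8 (100,000 binomial simulations each).

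**Step 5: DASH.** At f = 0.5 and q = 0.8, the groups differ by 0.0708 in palsy at presentation. The shift is 0.0708 × 20 = 1.42 points with no recovery. If the 70% recovery is complete by three months (timing not given), it is 1.42 × 0.3 = 0.42, or 0.42/6 = 7% of the planned difference. At q = 0.4 the shifts are −0.47 and −0.14; at q = 0.5 they are 0.

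**The case against.** The strongest reply is that this is detail a condensed article leaves to the full protocol or the case report form. Much of that reply has weight.

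- The list of complications is introduced as illustrative, and nine of its ten items have no definition there. The contrast with non-union is therefore weak evidence.
- The variable lists are not exhaustive. Activity level is in the propensity model but in neither the intrinsic nor the injury list, and identification of the radial nerve is recorded as an element of surgery. Palsy could sit under additional injuries, and the permissive 0.5 threshold would readily admit it as a covariate.
- Charts probably show onset, and no sentence tells staff to count a palsy that was already there.
- Exclusions 1 and 5 might keep some palsy patients out.

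Three things remain. Palsy is the only listed complication that the eligibility criteria expressly let in, so the conflict is between two stated provisions and is more than brevity. Reading exclusion 5 as barring palsy would make the exemption in exclusion 4 pointless. And even if additional injuries does capture palsy, that supplies no onset rule for the outcome; identification of the nerve at surgery does not record palsy and exists only for operated patients.

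A reader might infer that palsy is certainly unrecorded at baseline, or that the complication comparison is biased against one particular treatment. The article supports neither. It leaves room for a record, and it does not say how palsy affects the choice to operate.

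**Conclusion.** The point holds in a limited form. As written, palsy from the injury can be counted in the complication rate, and palsy before treatment is not named for adjustment.

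- **Inflation** of the palsy component follows whenever some palsies are present at injury. It is a factor of 2 if half are, which is assumed. The overall complication rate is inflated by less: about 1.1 to 1.7 times once non-union alone is added.
- **Between-group bias** is conditional. It is zero if palsy patients are operated as often as not. With half of palsies present at injury it is about ±1.2 points at 45% or 55% operated and ±7.1 at 20% or 80%. The 45–55% range is by fracture subclass, so it only suggests what might hold for palsy patients. Direction and size are unknown.
- **DASH** is little affected: 0.42 points at 80% operated with 70% recovered, on an assumed 20 points per palsy. A reader might conclude that the primary comparison is compromised; these figures do not support that.

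The matter bears mainly on one component of one secondary outcome and is of minor to moderate importance.

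**What to change.** 1. Add to the injury-related variables: radial nerve palsy before the start of treatment (yes/no, from the emergency department chart).
2. In the definition of complications, count only radial nerve palsy that is new or has worsened after the start of treatment. Report palsy at presentation by group in the baseline table.
3. Include palsy at presentation in the mixed model and in the propensity score.

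Exclusion 4 stays as it is.

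The cost is one field, which can also be filled from charts for patients already enrolled, one sentence, and one covariate in each model. No visit is added and eligibility does not change. There are two downsides. A palsy missed at presentation may be classed as new. If palsy patients are mostly treated one way, a few may find no close match: at f = 0.5 and q = 0.8, about 19 would be operated (23.6 × 0.8 = 18.9) against about 5 not (4.7).
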